## Abstract

**Background:**

Accumulating evidence suggests that additional dietary fiber supplements may significantly improve glycolipid metabolism and pregnancy outcomes in individuals with gestational diabetes mellitus (GDM). However, the therapeutic effects of xylose oligosaccharides and inulin (XOS inulin) in pregnant women have not been investigated. Moreover, the underlying mechanism behind the therapeutic effects of this type of dietary fiber is not clear. Our study aims to assess the effects of daily XOS inulin supplementation on glycolipid metabolism and elucidate the therapeutic mechanism through gut microbiota analysis.

**Methods:**

This study is an 8-week, parallel-design, open-label, three-arm, single-center randomized controlled trial. Eligible participants were pregnant women between 24 and 28 weeks of gestation, and they were diagnosed with GDM through an oral glucose tolerance test (OGTT). The participants in the three groups will receive nutrition education alone, nutrition education plus XOS inulin (XOS 2 g and inulin 10 g) 12 g/day, or nutrition education plus XOS inulin 24 g/day. Measurements will be taken at baseline, week 4, and week 8. The primary outcome will be the change in glycosylated serum protein (GSP), and the key secondary outcomes include changes in fasting glucose, fasting insulin (FINS), 2-h postprandial plasma glucose (2 h-PPG), HbA1c, total cholesterol (TC), triglycerides (TG), LDL cholesterol (LDL-C), HDL cholesterol (HDL-C), and changes in the gut microbiota.

**Discussion:**

This study will evaluate the therapeutic effects of XOS inulin supplementation on glycemic control, lipid metabolism, gastrointestinal function, and perinatal outcomes in GDM patients and their offspring. It also provides insight into the potential role of the gut microbiome as a target for enhancing the therapeutic efficacy of emerging treatments for GDM. All participants will receive comprehensive GDM nutrition education, promoting sustainable dietary modifications that optimize maternal metabolic health and fetal outcomes.

**Trial registration:**

Chinese Clinical Trial registry ChiCTR2200060117. Registered on 19 May, 2022.

**Supplementary Information:**

The online version contains supplementary material available at 10.1186/s13063-025-09080-6.

## Background and rationale {6a}

Gestational diabetes mellitus (GDM) is a state of hyperglycemia, discovered during pregnancy via routine screening between 24 and 28 weeks of gestation [1]. The results of prospective studies indicate that GDM can pose a series of Health risks, such as preterm delivery, macrosomia, cesarean, and type 2 diabetes, to offspring or mothers [2, 3]. According to the meta-analysis of Ye et al., the total incidence of GDM in Mainland China is 14.8% [4]. The incidence of GDM in older mothers (> 35 years) in China is 26.7%, which is approximately twice as high as that reported in younger women [4]. Since the number of elderly pregnant women is increasing, effective therapeutic management is urgently needed to reduce the risk of long-term chronic diseases.

As guidelines recommend, 70–85% of women with GDM can control their blood glucose in the normal range by changing their lifestyle [5]. As an important part of lifestyle management, dietary nutrition therapy is needed to improve outcomes for women and their offspring. Considering the different dietary patterns between China and Western countries, limiting carbohydrate intake was recommended by the Chinese Medical Association (CMA) [6]. Another suggestion is to consume enough dietary fiber (up to 28 g/day), which is supported by American doctors and their Chinese colleagues [6]. Some studies support the idea that the intake of large amounts of dietary fiber can reduce the risk of GDM [7, 8]. However, only a few studies have explored the effects of additional soluble dietary fiber supplements in treating GDM, and the therapeutic effects of soluble fiber remain controversial [9].

Inulin and xylose oligosaccharides (XOS) are two types of soluble fibers. Only one study investigated the effects of pure inulin supplementation in treating GDM; the decrease in HbA1c in the experimental group was greater than that in the control group, but the difference in the decrease of fasting glucose level between the two groups was not significant [10]. Daily inulin intake may have therapeutic effect on GDM. In another small trial, consuming XOS 6 g/day significantly reduced fasting blood glucose of pregnant women with high risk factors for GDM, but the difference in GDM incidence between the two groups was not statistically significant. It is reported that XOS promotes the proliferation of bifidobacteria at a rate 20 times higher than other functional oligosaccharides. The mechanism underlying these positive effects involve changes in the gut microbiota caused by XOS [11]. As a novel food, XOS is considered safe under the proposed uses and use levels [12]. Previous study reported that no diarrhea episodes occurred on the first day of consumption of 3–5 g/day of XOS, but diarrhea occurrence on the first day of consumption of 10–12 g/day XOS was 18–20% [13]. A survey of Chinese women with GDM during their second trimester revealed that their daily dietary fiber intake was found to be only 11.7 ± 4.7 g, and there remains a significant gap between this and the Chinese Nutrition Society’s recommended daily dietary fiber intake of 30–35 g [14]. Based on the aforementioned evidence, we proposed that supplementing with a mixture of inulin and XOS to meet the recommend dietary fiber intake may have a beneficial therapeutic effect in pregnant women with GDM. However, no clinical studies to date have specially investigated this particular intervention.

Our study is to assess the effects of mixed inulin and XOS (XOS inulin) supplementation on glycolipid metabolism and the gut microbiome. The evidence generated from this trial will inform us whether daily XOS inulin supplementation is a viable new dietary approach to treat GDM.

### Explanation for the choice of comparators {6b}

To determine whether a dose–response relationship exists between the dose of XOS inulin and blood glucose metabolism, two supplement doses, 12 g/day and 24 g/day, will be used in the two experimental groups.

### Objectives {7}

We hypothesize that daily XOS-inulin supplementation improves glycolipid metabolism in GDM patients via modulation of gut microbiota. We designed this trial to test the efficacy of daily XOS inulin supplementation after the diagnosis of GDM for improving glycolipid control and changing the gut microbiome compared with standard dietary education. We also want to study the effects of XOS inulin supplementation on pregnancy outcomes.

### Trial design {8}

This study is an 8-week, parallel design, open-label, three-arm, single-center randomized controlled superiority trial. The participant flow through the trial is described in Fig. 1. The study protocol was designed and developed in accordance with the Standard Protocol Items: Recommendations for Interventional Trials (SPIRIT) 2013 checklist [15] (see Additional file 1). This trial was registered in the Chinese Clinical Trial registry: ChiCTR2200060117 (May 19, 2022).

**Fig. 1 Fig1:**
[figure not shown]
Flow chart of trial design, participant recruitment, and follow-up (GDM, gestational diabetes mellitus)

### Study setting {9}

This trial will be carried out at the obstetric clinic of Qingdao Municipal Hospital, Qingdao, China.

### Eligibility criteria {10}

The inclusion criteria are as follows: (1) Pregnant women between 24 and 28 weeks of gestation, who were diagnosed with GDM through a routine 75 g of oral glucose tolerance test (OGTT) following the CMA diagnostic criteria if one or more values reached the following levels: fasting glucose ≥ 5.1 mmol/L, 1 h ≥ 10 mmol/L, and 2 h ≥ 8.5 mmol/L [13], (2) participants with singleton pregnancies, (3) patients treated with medical nutritional therapy, without insulin or other antidiabetic drugs, and (4) patients who signed an informed consent or whose guardian signed for them.

Participants will be excluded if they meet the following criteria: (1) were hospital inpatient with severe diseases; (2) had pregnancy induced diabetes mellitus; (3) had GDM and accepted hypoglycemic drug therapy or insulin injection; (4) did not receive prenatal care at Qingdao Municipal Hospital; (5) have consumed dietary fiber, probiotics, or prebiotic products in the past month; (6) have a history of surgery that would result in a change in the typical structure of the gastrointestinal tract, or have organic lesions of the intestine, or acute or chronic intestinal obstruction; and (7) have diseases that make them unsuitable for participation in this clinical trial.

### Interventions {11a}

All participants in the three groups will receive individualized dietary advice in line with updated guidelines issued by the ADA and CMA [5, 16]. First, women will be encouraged to eat at least 1600 cal daily to reduce the incidence of ketosis. Second, participants will be asked to consume a minimum carbohydrate intake of 175 g per day, mostly from low glycemic sources, distributed across the day over three meals and three snacks. Third, the intake of milk (500 g/day) and the amounts of fish, poultry, eggs, and lean meat should be increased by 50 g/day. We will also list the specific types of food that are suitable to eat. GDM participants will also be equipped with other effective skills, such as exercising, performing self-blood glucose monitoring, and keeping daily food diaries. All education will be conducted by experienced registered dietitians.

After collecting baseline data, women in one of the two fiber groups received two or four boxes of soluble dietary fiber (Nutrasumma, Qingdao Nutrasumma Health Technology Co., Ltd.) every month. Each box contains 15 bags (12 g/bag) of soluble dietary fiber (XOS inulin). The dietary fiber can be dissolved in warm water and has a mildly sweet taste after dissolving. Fiber group 1 will take one bag (12 g) daily, while fiber group 2 will take two bags (24 g) daily, with both groups dissolving the fiber in warm water each morning.

### Criteria for discontinuing or modifying allocated interventions {11b}

Participants can withdraw from the trial or modify allocated interventions at any time for any reason. The investigator may discontinue patients from the trial to protect their safety or if they are unable or unwilling to continue with the trial (such as pregnancy occurs during trial participation). If adverse event is reported, doctors will also assess the patient to determine whether they should be withdrawn from the study or modify allocated interventions. The reason for each patient’s withdrawal, especially the occurrence of any adverse events, will be explained in detail.

### Strategies to improve adherence {11c}

Participants must return all the product containers every month to assess compliance and actual soluble dietary fiber intake. Adherence to the assigned treatments will be assessed through the use of a daily calendar during each phone call and by counting the returned packs at the end of the trial. Compliance rate will be calculated using the following formula: compliance rate = (packs taken/packs prescribed) × 100. A compliance rate below 80% will be classified as poor compliance.

### Relevant concomitant care permitted or prohibited during the trial {11d}

During the trial, participants will be prohibited from taking self-administered probiotics, dietary fiber supplements, antibiotics, or any other food/medication that may interfere with study outcomes.

### Participant timeline {13}

The protocol flow chart and timeline of the study are illustrated in Fig. 1 and, respectively.

### Sample size {14}

HbA1c monitors the exposure to circulating glycemia in the previous 3 months, whereas glycosylated serum protein (GSP) represents glycemia for 2–3 weeks [17–19]. Because this trial will last for 4 to 8 weeks, we chose the change in GSP as the primary endpoint, which may be more reliable. Since no previous studies assessed soluble fiber supplements for GSP in GDM patients, we calculated the sample size for HbA1c. In an inulin supplementation trial by Miao et al., a difference in HbA1c reduction of 0.27% was observed between the control group and the10 g/day inulin supplemented group [10]. We referred to the results of this trial, showing that an *n* = 37 would provide 90% power at an alpha level of 0.05. Allowing for a 20% dropout, a total sample size of 135 (45 per group) allows for an adequate sample size for our trial.

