### Outcomes {12}

The primary outcome measure will be the Change in GSP after 8 weeks of treatment across the different groups. GSP is a sensitive indicator of blood glucose levels in the last 3 weeks, making it particularly useful for monitoring pregnant women with diabetes. According to Morris et al., GSP levels correlate strongly with short-term glycemic control (fasting glucose: *r* = 0.798; postprandial: *r* = 0.846) and are measured via affinity chromatography targeting glycated serum proteins. This method allows frequent assessment of diabetic control, addressing the need for rapid treatment adjustments during pregnancy [20]. Secondary outcomes include fasting plasma glucose, 2 h-PPG, FINS, HbA1c, TC, LDL-C, HDL-C, TG, Wexner constipation score (WCS), the Bristol Stool Form Scale (BSFS), pregnancy outcomes, and changes in gut microbiota. Fasting venous blood will be collected at baseline (week 0), week 4, and trial completion (week 8). Blood samples will be processed within 2 h of collection (30-min room-temperature clotting, centrifugation at 3000 × g for 15 min), with serum/plasma aliquots stored at −80 °C. The Clinical Laboratory Department of Qingdao Municipal Hospital will test all the above laboratory indicators.

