### Statistical analysis {20a}

Statistical analyses will be performed using the R 4.3.0 software. The Shapiro–Wilk test will be used to check for a normal distribution of the data. Continuous variables with a normal distribution will be presented as the mean (standard deviation [SD]); non-normal variables will be reported as the median (interquartile range [IQR]). Categorical data will be compared among the three groups using chi-square tests and partitions of the chi-square method. Linear models will be used to compare the mean values of the outcome variables among the three groups, adjusting for baseline values (e.g., age, BMI, nationality, gestational weeks, calorific intake). GSP Changes from baseline to week 8 will be analyzed using mixed-effects models with treatment group, time, and group × time interaction as fixed effects, adjusting for baseline GSP. *P*-value of less than 0.05 will be considered statistical significance. Post hoc pairwise comparisons were adjusted using the Bonferroni method to reduce the probability of type I error.

We will evaluate gut microbial diversity through complementary alpha- and beta-diversity analyses. For alpha diversity (within-sample microbial complexity), we will calculate three complementary metrics: Chao1 index (quantifying species richness), Shannon index (reflecting both richness and evenness), and Simpson index (measuring dominance of abundant species). Alpha-diversity differences between groups will be assessed using the Wilcoxon test. The cross-sectional difference in beta diversity (between-sample compositional differences) between the groups will be assessed by permutational analysis of variance (PERMANOVA) of Bray–Curtis dissimilarity and illustrated by PCoA models [35]. The significant bacterial taxa responsible for discrimination between the three groups will be identified via linear discriminant analysis (LEfSe) with linear discriminant analysis (LDA) [36]. Some multiple comparisons, such as differential abundance analysis of the microbiota, will be corrected using the Benjamini–Hochberg false discovery rate (FDR).

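### The 90% power applies to one HbA1c comparison without multiplicity adjustment; it does not carry over to the Bonferroni-adjusted pairwise comparisons, and no power or detectable difference is given for GSP

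*Protocol article*

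**What the plan says.** The Sample size section prefers GSP to HbA1c for a trial of this length: "we chose the change in GSP as the primary endpoint, which may be more reliable". The Outcomes section confirms it: "The primary outcome measure will be the Change in GSP after 8 weeks of treatment across the different groups". Because no earlier study had assessed soluble fiber for GSP in GDM, the authors state that "we calculated the sample size for HbA1c".

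The effect comes from an earlier inulin trial, in which "a difference in HbA1c reduction of 0.27% was observed between the control group and the10 g/day inulin supplemented group". On that basis 37 per group "would provide 90% power at an alpha level of 0.05". The section gives no SD, does not say whether the test is one- or two-sided, and mentions no multiplicity adjustment. After an allowance of 20% for dropout it arrives at 45 per group, 135 in all, and calls this adequate for the trial.

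The Statistical analysis section plans a mixed-effects model for GSP change with group, time and their interaction, adjusted for baseline GSP, with significance at P below 0.05. It adds: "Post hoc pairwise comparisons were adjusted using the Bonferroni method to reduce the probability of type I error". It does not say how many pairs are adjusted.

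**The concern.** The power statement and the analysis do not describe the same test. The first is for two groups, HbA1c and alpha 0.05. The statements a reader will want from this trial are whether 12 g/day beats control and whether 24 g/day beats control, on GSP, and these are judged at a stricter Bonferroni level.

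If the 90% is taken at face value, a non-significant result for either dose would be read as stronger negative evidence than the design supports. In addition, calling 135 adequate for a trial with GSP as primary endpoint has no stated GSP difference behind it.

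**Working it through.** **Inputs.** From Sample size: 37 per group (read as per group because 45 per group follows from it), 90% power, alpha 0.05, HbA1c difference 0.27%, 20% dropout, 45 per group. From Statistical analysis: Bonferroni on pairwise comparisons. Assumed, because not stated: two-sided tests, and either three adjusted pairs (all pairs of three arms) or two (each dose against control).

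**1. The plan's own figure.** Without an SD, 37 cannot be reproduced independently. It can be inverted for the standardised difference d it implies.
- Normal approximation: d = (1.960 + 1.282) × √(2/37) = 0.754, so SD = 0.27/0.754 = 0.358.
- Noncentral t with 72 df: power is 90% at d = 0.764, so SD = 0.27/0.764 = 0.353.

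The loss of power below depends only on d and not on the missing SD.

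**2. Numbers left after dropout.** 45 × 0.8 = 36 per arm.

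**3. Power per pairwise comparison, no baseline adjustment.** The noncentrality is d√(n/2): 0.764 × √18.5 = 3.286 with 37 per arm and 0.764 × √18 = 3.241 with 36. Power is the probability that a noncentral t exceeds the critical value at the adjusted level.

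| Level per comparison | Critical t (n = 37) | 37 per arm | 36 per arm |
|---|---|---|---|
| 0.05, unadjusted | 1.993 | 90.0% | 89.2% |
| 0.05/2 = 0.025 | 2.289 | 83.8% | 82.7% |
| 0.05/3 = 0.0167 | 2.451 | 79.6% | 78.2% |

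The normal approximation with d = 0.754 gives 80.2% and 78.9% in the last row. If the sizing was one-sided, the picture is much the same: d = (1.645 + 1.282) × √(2/37) = 0.680, and at one-sided 0.05/3 power with 37 per arm is Φ(0.680 × √18.5 − 2.128) = Φ(0.80), about 79%.

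**4. Overall three-group test at 0.05.** A one-way F test serves as a proxy for the omnibus test in the mixed model, with noncentrality n × Σ(μᵢ − μ̄)² in SD units.
- Both fiber arms at the full effect: 92.8% (37 per arm) or 92.1% (36).
- Lower dose at half the effect: 83.5% or 82.4%.

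**5. Joint outcomes, three pairs adjusted.** By simulation with the pooled variance and both fiber arms at the full effect, 37 per arm: each comparison with control 80%, at least one 91%, both 69%. With 36 per arm: 79%, 90% and 67%.

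**6. Effect of adjusting for baseline.** With equal variances at the two times and baseline-to-follow-up correlation r, the change score has variance 2σ²(1 − r) and the baseline-adjusted outcome σ²(1 − r²). The ratio is (1 + r)/2, so d becomes d/√((1 + r)/2). At 0.05/3 with 37 per arm, power is 94.5% for r = 0.3, 90.7% for 0.5, 86.4% for 0.7 and 84.1% for 0.8. The protocol gives no r; these values only show the range.

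**7. GSP.** Solving the same formula for d with 36 per arm at 0.05/3 gives a detectable difference of 0.88 SD with 90% power and 0.78 SD with 80%, in SDs of GSP change and before baseline adjustment. This needs no earlier GSP data.

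**The case against.** The strongest reply is that Bonferroni applies only to post hoc pairs, while the mixed model is tested at 0.05. That stands: the overall test has about 82–93% on the borrowed effect, and at least one adjusted comparison with control succeeds about 90–91% of the time. A reader might infer that the planned three-arm analysis as a whole has only 79–80% power, or that the trial's false-negative risk is 20%. The protocol does not support this; those figures belong to one named pair. But an overall result does not say which dose works, and the effect used for sizing is itself pairwise.

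Second, three pairs is an inference. The dose-response aim makes it plausible, but the text gives no number. With two pairs the figure is 83–84%, still below 90%.

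Third, baseline adjustment may recover the loss. This also stands, and it is not cancelled by the 0.27% being a difference in reductions, since adjustment improves on a change score. The unadjusted figures are therefore a floor under equal variances, and the gain cannot be computed from the protocol.

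Fourth, the use of HbA1c is openly stated and explained. A reader might infer that 90% is claimed for GSP, or that GSP power is very low. Neither follows: no such claim is made, and a low figure would need an assumed GSP effect for which the protocol has no basis. What remains is that 135 is called adequate with no detectable GSP difference given.

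Finally, the effect is back-solved from the stated 37 and 90%, so it cannot test whether 37 was calculated correctly. It shows only what the stated power becomes at a stricter level.

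**Conclusion.** The point holds as a mismatch between the stated power and the adjusted pairwise comparisons. It is not a demonstrated arithmetic error. On the plan's own implied effect and two-sided testing, power per comparison before baseline adjustment falls from 90% to about 80% (78% with 36 per arm) for three pairs, or to about 83–84% for two. The drop does not depend on the unstated SD. It does depend on the number of pairs and may be partly or wholly offset by adjustment for baseline GSP. All these figures are on the HbA1c effect; for GSP the protocol supplies neither power nor a detectable difference.

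**What to change.** Reword the Sample size section; no extra patients are needed. It should say that:
- 90% power with 37 per group applies to a single HbA1c comparison without multiplicity adjustment;
- for the Bonferroni-adjusted pairwise comparisons, power before baseline adjustment is about 80% if three pairs are adjusted or 83–84% if two are, and which of these is planned;
- for GSP change, 36 per arm at 0.05/3 detects about 0.88 SD with 90% power or 0.78 SD with 80%, before baseline adjustment.

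The cost is a few sentences and a less favourable stated power.

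Testing the two comparisons with control in a fixed order, each at 0.05, would keep the 90% for the first one. It is optional and a trade-off: the second cannot be claimed if the first fails, and a sequence limited to those two leaves out the comparison between doses, which bears on the dose-response aim.

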### Allocation: sequence generation {16a}

Eligible patients will be randomized into three groups: The nutrition education group (*n* = 45, accept nutrition education of GDM), fiber group 1 (*n* = 45, receive nutrition education of GDM plus 12 g/day mixed soluble fiber, which contains 2 g of XOS and 10 g of inulin), and fiber group 2 (*n* = 45, accept nutrition instruction of GDM plus 24 g/day mixed soluble fiber, which contains 4 g of XOS and 20 g of inulin). Simple randomization with a 1:1:1 allocation ratio will be performed using a computer-generated random number sequence.

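### At the stated 20% dropout, 45 per group leaves 36 completers, one fewer than the 37 the protocol says it needs; the effect on power is minor

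*Protocol article*

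**What the plan says.** The protocol article, Sample size {14}, takes its effect from a published inulin trial in which "a difference in HbA1c reduction of 0.27% was observed between the control group" and a group given 10 g/day of inulin. From this it states that n = "37 would provide 90% power at an alpha level of 0.05". The next sentence reads "Allowing for a 20% dropout, a total sample size of 135 (45 per group"), and calls that size adequate for the trial.

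The section does not label 37 as per group. It gives no SD, does not say whether alpha is one- or two-sided, and does not show how the dropout allowance was applied. Allocation: sequence generation {16a} repeats n = 45 for each of the three arms, allocated 1:1:1. Nothing elsewhere in the article changes or explains these figures.

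**The concern.** A dropout allowance has one purpose: once the stated share of participants is lost, the required number should remain. Here the required number, the dropout rate and the number randomised all stand in two adjacent sentences, and the third does not follow from the first two. The allowance is also the only reason the article gives for going from 37 to 45, and readers and the final report will rely on it. At stake is whether the stated property, 90% power after 20% dropout, is delivered on the protocol's own terms.

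**Working it through.** **Inputs, all from Sample size {14}:** required n = 37; power 90%; alpha 0.05; dropout 20%; planned 45 per group, 135 in total.

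**Step 1. Is 37 per group?** If 37 were a total, a 20% allowance could not lead to 45 in each of three arms. Only the per-group reading fits.

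**Step 2. Reproduce the stated figure.** Multiplying by one plus the dropout rate: 37 × 1.2 = 44.4, rounded up to 45; 45 × 3 = 135. This matches both published figures. The article states no formula, so this route is an inference.

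**Step 3. Test the claim directly.** This step does not depend on how 45 was reached.
- Completers per group: 45 × 0.80 = 36, against 37 required.
- In total: 135 × 0.80 = 108, against 3 × 37 = 111.

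**Step 4. The number that would meet the claim.** Required n divided by (1 − dropout):
- Per group: 37 / 0.80 = 46.25, rounded up to 47. Check: 47 × 0.80 = 37.6, which is at least 37. Three groups: 47 × 3 = 141.
- Inflating the total instead: 111 / 0.80 = 138.75, so 139. This is also above 135.

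**Step 5. The dropout that 45 does cover.** 45 − 37 = 8 losses per group; 8 / 45 = 17.8%.

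**Step 6. The cost in power.** No SD is given, so the standardised difference d has to be back-solved. These are assumptions: a two-sided two-sample comparison at alpha 0.05, with no adjustment for multiple comparisons.
- If exactly 37 per group gives exactly 90%, a t-test implies d of about 0.764. With 36 per group, power is then 89.2%. The normal approximation gives an SD of 0.27 / [√(2/37) × (1.960 + 1.282)] = about 0.358, and also 89.2% at 36.
- If 37 was itself rounded up from just above 36, d is about 0.774, and 36 per group gives just under 90%.

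| Assumption behind 37 | d | Power with 36 per group |
|---|---|---|
| 37 gives exactly 90% | about 0.764 | 89.2% |
| 37 rounded up from just above 36 | about 0.774 | just under 90% |

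The loss from the dropout arithmetic is therefore between about 0 and 0.8 percentage points. A one-sided test, under the normal approximation, gives 89.3% in place of 89.2%.

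**The case against.** The strongest objection is that the shortfall makes no practical difference: one completer per arm, at most 0.8 points of power, and no change to design, analysis or enrolment. That stands, and it sets the weight of the point. It does not make the sentence correct.

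A second objection is that a dropout is not wholly lost to the analysis. GSP is also measured at week 4, the primary model is a mixed-effects model adjusting for baseline GSP, and missing data are to be imputed under ITT. A woman who leaves after week 4 still contributes. This stands too: 36 completers may carry more than 36 patients' worth of information, by an amount the documents do not allow us to estimate. It would be wrong to say that imputation restores nothing. But the Sample size section makes its own allowance for dropout and does not claim that imputation offsets it.

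Third, the 37 was derived for HbA1c, whereas the primary outcome is GSP. A difference of one patient therefore says little about power for the actual primary endpoint. That is a fair limit on the power figures; the mismatch between 37, 20% and 45 is unaffected.

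A reader might also infer that dropout brings power down to about 78%, because the post hoc pairwise comparisons are to be Bonferroni-adjusted. The documents do not support that reading. At alpha 0.05 / 3 = 0.0167 and d of about 0.764, 36 per group gives 78.2%, but the full 37 already gives 79.6%. So about 10.4 of the 11.8 points come from the adjustment and only about 1.4 from the missing completer. Dividing by three also assumes that all three pairwise comparisons count, and the Sample size section claims no adjusted power. Multiplicity is a separate matter.

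**Conclusion.** The point holds as a small arithmetic error. On the protocol's own figures, 45 per group does not cover 20% dropout from a requirement of 37: it leaves 36, and 47 per group (141 in total) would be needed. This rests only on reading 37 as per group.

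The consequence is minor: about 89% to 90% power in place of 90% for a single unadjusted comparison, before any recovery through the mixed model or imputation. That range depends on the assumed two-sided test and the back-solved effect size. Whether 37 is itself right cannot be checked without the SD. Multiplication by 1.2 is the likely cause but is not documented. The error does not threaten the trial's conclusions.

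**What to change.** Keep 135 and correct the one sentence in Sample size {14}. Either of these would be accurate:

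- 45 per group keeps 37 completers with up to 8 losses per group (17.8% dropout).
- With 20% dropout, 36 per group remain, giving about 89% power for a single unadjusted comparison under the sample-size assumptions.

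If the second is used, state the SD and the sidedness behind the 37, since the power figure depends on them. Labelling 37 as per group would remove the remaining ambiguity. The cost is one edited sentence, with no additional participants and no change to the allocation or the analysis.
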